**Figure 1 F1:**
[figure not shown]
The flow diagram of the study protocol.

**Figure 2 F2:**
[figure not shown]
**Timeline of baseline and follow-up data collection.** MVPA = moderate-to-vigorous physical activity measured using accelerometers; Q = questionnaire measures of motivation towards physical education, and perceived teacher autonomy support.

### Participants

Secondary 3 to 4 students (typically 14 to 15 years old) from local Hong Kong schools (i.e., Cantonese speaking, with vast majority of students being Chinese) will be recruited to take part in the study. All classes included in the trial will be taught by different PE teachers. Students will need to complete the Physical Activity Readiness Questionnaire [20] to assess their physical health and readiness to take part in physical activity. Based on the response to the questionnaire, students having no known undesired physical reactions (e.g., chest pain, dizziness, joint problems) to physical activity will be considered eligible to take part in the current study. Written informed consent will be obtained from participating students and a parent or guardian prior to data collection.

Students will be recruited from schools that meet our eligibility criteria. Specifically, schools will be eligible if (a) they are co-educational (i.e., mixed-sex); (b) they are located in areas of lower-half of the socioeconomic classes within Hong Kong, as defined by the 2011 census [21]; (c) they have a unisex PE lesson policy (applies to most schools in Hong Kong to increase generalizability). Baseline (i.e., pre-randomization) and post-test (i.e., post-randomization) data collection will be conducted during PE lessons. Pre-randomization data collection will begin in September 2013; whereas the post-test data collection will begin in October 2013.

### Intervention

A 4-hour workshop will be provided to teachers of classes allocated to the experimental group. The goal of the workshop is to teach PE teachers basic rope skipping skills, and to demonstrate how the intervention could be delivered in their classes. Rope skipping ambassadors will also attend the workshop to familiarize themselves with the teachers and the structure of the 15-minute activity. The workshop will be led by a professional rope skipping coach (“the coach”), who has experience as a full-time school PE teacher, and therefore understands how typical PE lessons in Hong Kong are structured.

The workshop will consist of four sections. In the first section, teachers will be taught rope skipping techniques. These techniques will be included in the two 15-minute rope skipping activities proposed to teachers. In the second section of the workshop, the coach will demonstrate two 15-minute rope skipping routines that could be implemented by teachers during their lessons in the intervention period. In this session, teachers will be asked to follow the routine led by the coach. The goal of this task is to help teachers understand how the intervention could be implemented, and to experience the intervention from a student’s perspective.

In the third section of the workshop, the coach will discuss with teachers good and poor practice when conducting the intervention, in terms of how to maximize students’ physical activity within the 15-minute rope skipping activity period. The good and bad practices to be highlighted were derived based on discussions between the lead author, a co-author, and the coach. Videos demonstrating these practices will be shown to teachers to assist in the discussion. Videos of good practices will feature the coach teaching one technique by 1) breaking down complex skills (e.g., normal rope skipping) into series of simpler skills (e.g., skipping without the rope); 2) allowing students to adjust to different levels of difficulty; 3) helping students develop the skill by drawing on their previous rope skipping skills and experiences. These practices will encourage students of lower abilities to remain engaged in physical activity. In contrast, the video showing poor teaching practices will feature the coach 1) spending too much time teaching verbally when students stand or sit still; 2) teaching a skill that may be too difficult for most students. The two sets of practices were pilot tested on two groups of three students each. Students who were taught using the good practices exercised in MVPA for 57.5 ± 3.5 percent over a five-minute period. In contrast, students taught using the bad practices spent 20.8 ± 3.6 percent of the five-minute period in MVPA.

In the fourth section of the workshop, the lead author and the rope skipping coach will lead discussions about potential challenges teachers may face when conducting the intervention, and ways to overcome these obstacles. Teachers will be encouraged to contribute to the discussion by reflecting on their experiences in teaching rope skipping or similar activities at their respective schools and during the workshop. They will be encouraged to identify potential barriers and solutions for delivering the intervention in their schools, or how to overcome any minor incidents they can foresee. The goal of the discussion is to ensure all teachers have similar knowledge and expectations for conducting the rope skipping activity, and therefore reduce the discrepancies in the actual implementations of the activity.

The intervention in schools will involve a 15-minute rope skipping activity that is implemented by the class PE teacher at the start of four consecutive PE lessons (during post-test periods). After the rope skipping activity, a usual lesson as run by the PE teacher will be resumed. A four-lesson duration was chosen because, following Hong Kong governmental guidelines [22], the typical length of teaching an activity during PE (i.e., a unit) is four lessons. In the first two lessons of the four-lesson post-test period, a skipping ambassador [12] will be sent to each class to demonstrate rope skipping skills, and assist the teacher in running the 15-minute activity and instructing students. In the second to lessons, the teacher will lead the rope skipping activity. A wait list control group will be adopted in the study. That is, classes allocated in the control group will receive the intervention after the end of the study period.

### Fidelity of intervention

Teachers in the experimental group will be asked not to discuss the content of the workshop with control group teachers whom they may encounter. To ensure intervention fidelity (experimental group) and test for any contamination effects (control group), raters blinded to study hypotheses will observe all PE lessons run by each teacher (including those assisted by the skipping ambassadors) during the study period. The System for Observing Fitness Instruction Time (SOFIT) [23,24] will be used by the rater to record the activities students engaged in during each lesson, the lesson context, and teacher involvement. Additional to the SOFIT protocol, the raters will also need to report whether students were engaging in activities related to rope skipping. Raters will record the specific start and finish times of rope skipping activity. They will be asked to mark the time (to the closest second) based on a web-based clock showing the official time of Hong Kong, provided by the Hong Kong Observatory. The computer used to initialize the accelerometers will also be synchronized to the same time. Raters without an internet-enabled mobile phone will need to report the offset of their time-telling device with the official time when they return the accelerometers and records to the investigators.

Raters will be university students from a Hong Kong university. They will receive a 2-hour training session led by the lead author and a co-author, based on the SOFIT training manual [24]. Video recordings of PE lessons, for classes in both experimental and control groups, during the intervention period will be taken. Each class will be video-recorded at least once during the post-test period. At least one rating made by each rater will be cross-checked by an investigator of the study using the recorded videos clips. These ratings will be used to examine the inter-rater/class reliability.

### Outcomes

#### Primary outcome

The primary outcome of the study is the proportion of PE lesson students spend in MVPA. This will be measured using ActiGraph (Pensacola, Florida) GT3X + accelerometers. MVPA will be defined using Evenson and colleagues’ criteria [25], and 1-second epochs will be used [26]. Evenson et al.’s cutoff values were chosen because they were found to be more accurate than other commonly used cut points [27]. To test the validity and sensitivity of the devices of capturing non-lateral movements such as rope skipping, we invited 12 boys and girls with varying rope skipping experience perform rope skipping tricks (in 1-minute bouts with at least one minute rest in between) that will be included in the intervention while wearing accelerometers. For all skippers and for all tricks tested, the activity was classified as MVPA based on Evenson et al.’s cut points. In our formal trial, accelerometry measurements will be taken during the first three lessons at baseline (Lessons 1 to 3; see Figure 2). MVPA will be measured for the same sets of seven students in each class throughout the study. These students will be randomly selected by the investigators from class lists (not containing names of students) provided by teachers using a random number generator. The mean of each student’s proportion of time spent in MVPA during these three classes will be used as his or her baseline. The primary outcome will pertain to the individual level and will not be aggregated within the cluster.

After baseline assessments, classes will be randomized into either the experimental or the control group. Teachers of classes in the experimental group will be invited to attend the teacher workshop after Lesson 4, and before Lesson 5. Following the workshop, these teachers will implement the intervention in their class for four consecutive PE lessons (Lessons 5 to 8). For schools in the control group, teachers will conduct classes using their usual methods, which are not expected to include rope skipping. Post-test accelerometry measures will be taken during Lessons 5 to 7. The mean of each student’s MVPA percentages taken from these three classes will be used as follow-up scores. Similarly, this measure pertains to the individual level.

#### Secondary outcomes

Secondary outcomes include students’ time spent in sedentary, light, moderate, and vigorous physical activity as measured by accelerometry, and defined using Evenson et al.’s [25] cut-points. Perception of autonomy support provided by their teachers during the last four PE lessons, and their motivation (autonomous and controlled) during the last four PE lessons were also measured as secondary outcomes. Psychological variables will be measured using self-reported questionnaires administered using pen and paper at the end of Lesson 4 (baseline) and Lesson 8 (post-test). Specifically, the 6-item version of the Learning Climate Questionnaire [28] will be used to measure students’ perceived autonomy support provided by their teachers. The original scale in English was translated into Chinese using a back-translation protocol. As the translated scale has not previously been used, factorial validity of responses will be examined before the main analyses are conducted. In terms of motivation orientations, the Chinese Perceived Locus of Causality Questionnaire (PLOCQ) [29] will be used to measure autonomous and controlled motivation. Evidence of validity and reliability of the scale scores has been shown by Lonsdale et al. [29]. As motivational factors are likely to differ across individuals, students’ motivation towards PE was considered as a variable at the individual level. In contrast, as perceived autonomy support is referenced to the same teacher, the mean scores within each cluster will be aggregated to form an indicator representing this construct at the cluster level.

### Sample size

Sample sizes were calculated based on the effect sizes calculated from Lonsdale et al.’s [6] systematic review and meta-analysis. In their study, Lonsdale et al. found that the standardized difference, or Cohen’s *d*, of fitness infusion interventions implemented within PE classes to be 1.4. Adopting a conservative approach, we based our power calculation on a projected effect of *d* = 1.0. The required sample size was calculated using GPower 3.1, with alpha level set to .05, and power at .80. The required sample size for a two-tailed independent sample t-test was found to be 34 students.

To account for the clustering nature of the data, the required sample size of 34 was adjusted by design effect [30] of 1 + (*m*-1)ρ, where *m* is the sample size of each cluster and ρ is the intraclass coefficient (ICC). In order to limit the disruptions to classes when distributing accelerometers, we decided to administer the device to seven students in each class. Aelterman et al. [15] found in their study that the ICC of MVPA between classes was .63. Using these estimates, the required correction factor is 1 + (7–1).63 = 4.78, meaning that the total required sample size is 163 (4.78 × 34 students). Therefore, 24 classes will need to be recruited for the study (24 classes × 7 students = 168 students).

### Randomization

#### Sequence generation

Randomization and allocation to experimental and control groups will be conducted after baseline measures are taken. Matched-pairs cluster randomization will be used. That is, randomization and group allocation will be conducted at the cluster (i.e., class) level, Specifically, participating classes will be matched in comparable pairs in terms of 1) class gender, 2) students’ percentage of time spent in MVPA measured at baseline, and 3) whether rope skipping is included in the school’s original PE curriculum. Baseline measures will be dummy coded and sent to a statistician outside the research group, who will then randomize and allocate classes in experimental and control groups. This person will have no information regarding the participating schools or classes. The statistician will match the pairs and randomize classes into experimental and control groups using a random number generator. After randomization, teachers will be told the group allocation of their classes. The allocation mechanism, however, will be concealed to them.

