### Statistical methods

Multilevel modeling will be used to account for the effects of participant clustering. Specifically, a three-level (time within student within class) model will be examined. For our primary outcome of students’ percentage time spent in MVPA, the effects of group allocation and student gender on percentages of time spent in MVPA will be examined using a multilevel regression model. The group × gender interaction effect will also be examined to determine whether the effect of the intervention is homogeneous across genders. Further, we will also examine a model by adding perceived autonomy support, autonomous and controlled motivation as potential confounders of the outcome. Two-tailed tests with an alpha level of .05 will be used to determine the significance of all results. To examine whether the intervention would lead to changes in motivation variables and perceived autonomy support by teachers, these variables will be regressed on group, gender, and group × gender in an additional series of three-level regression analyses. Statistical analyses of the study will be conducted by a statistician blinded to the hypotheses of the study and to each class’ allocation to the experimental or control condition.

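### Classes are randomised in matched pairs, but the stated model contains neither the pair nor the curriculum indicator, so it takes no credit for the matching and is conservative if the matching works

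*Protocol article*

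**What the plan says.** **Randomisation.** Under Sequence generation the protocol article says "Matched-pairs cluster randomization will be used". It adds that "participating classes will be matched in comparable pairs in terms of 1) class gender", with two further criteria: "percentage of time spent in MVPA measured at baseline" and "whether rope skipping is included in the" school's own PE programme. With 24 classes this gives 12 pairs.

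**Analysis.** Under Statistical methods: "Specifically, a three-level (time within student within class) model will be examined". The effects named for the primary outcome are group, student gender and group × gender. A further model adds autonomy support and the two motivation scores. The section mentions neither pair nor curriculum, and names no time or group × time term.

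**Role of baseline.** The abstract (Methods/Design) says effectiveness will be judged by comparing changes from baseline to follow-up between the groups. Primary outcome reduces each phase to one mean per student, so the time level is most naturally read as baseline versus follow-up.

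**Sample size.** The calculation takes a "projected effect of *d* = 1.0", "with alpha level set to .05, and power at .80", and reports: "The required sample size for a two-tailed independent sample t-test was found to be 34 students". A design effect then leads to 24 classes.

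**The concern.** When randomisation is done within pairs, the treatment comparison is a within-pair comparison. Effective matching makes the two classes of a pair alike, which reduces the true variance of the estimated effect. An analysis that ignores the pairs estimates its error from all the variation between classes, including variation between pairs that the design has already removed. Its confidence interval is then wider than it need be and its test rejects too rarely under the null.

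This is more than condensation in a journal article. Statistical methods names the levels, the fixed effects and the extra covariates, and adjusts for psychological scores, yet omits the structure by which classes are allocated. With only 24 clusters the choice can affect the result, and leaving it open allows it to be made after the data are seen.

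**Working it through.** **Inputs from the protocol article.** d = 1.0, two-sided alpha .05, power .80, ICC .63, 7 students per class, 24 classes, 1:1 allocation.

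**Assumptions (not in the article).** Within-pair correlation r of class means, 0 to .5. Class-level correlation between baseline and follow-up, .3 to .9. Student-level correlation .5. Total SD 1.

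**1. The plan's own figure.** An independent-samples t-test with d = 1.0 has power 78.1% at 16 per arm and 80.7% at 17, giving 34 students. The design effect is 1 + (7 − 1) × .63 = 4.78. Then 34 × 4.78 = 162.5, rounded up to 163, and 162.5 / 7 = 23.2, rounded up to 24 classes. The figure reproduces.

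On class means, the variance is .63 + .37/7 = .683. The SE of the group difference is √(.683 × 2/12) = .337, and power on 22 df is 80.9%.

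**2. The same comparison analysed in pairs.** The variance is multiplied by (1 − r), and df fall to 11. An unpaired SE exceeds the paired one by 1/√(1 − r).

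| r | SE ratio | Paired power, 12 pairs | Classes for 80% |
|---|---|---|---|
| 0 | 1.00 | 77.0% | 26 |
| .1 | 1.05 | 81.1% | 24 |
| .2 | 1.12 | 85.4% | 22 |
| .3 | 1.20 | 89.6% | 20 |
| .5 | 1.41 | 96.7% | 16 |

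Pairing breaks even at r of about .1, and 24 classes suffice from there upwards. This table is for a single set of class means (follow-up only), not for change.

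**3. Change from baseline, the comparison in the abstract.** In 4,000 simulated trials per setting, 24 class means (12 per gender) were paired on baseline within gender, randomised within pair and analysed with and without the pair. As a check on the unpaired SE, the variance of a class-mean change is 2 × [.63(1 − ρ) + (.37/7)(1 − .5)], where ρ is the class-level correlation. At ρ = .5 this is .683, so the SE is √(.683 × 2/12) = .337; the simulation gave .339.

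| Class-level correlation ρ | .3 | .5 | .7 | .9 |
|---|---|---|---|---|
| Change, no pair: SE from model | .397 | .339 | .268 | .173 |
| Change: true SE | .327 | .302 | .248 | .166 |
| Ratio | 1.21 | 1.12 | 1.08 | 1.04 |
| Change, no pair: type I error | 2.0% | 2.8% | 3.8% | 4.5% |
| Change, no pair: power | 70% | 83% | 96% | 100% |
| Change, with pair: power | 79% | 86% | 96% | 100% |
| Follow-up with class-mean baseline covariate: type I error | 5.1% | 5.1% | 5.4% | 5.1% |
| Follow-up with class-mean baseline covariate: power | 84% | 90% | 97% | 100% |

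The simulation error of a 5% rate is √(.05 × .95/4000) = 0.3 percentage points.

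**4. Dependence on the random effects.** Suppose the three-level model had random intercepts only, without class-by-time variation. The group × time SE would be √{[.63(1 − ρ) + .37 × .5] × 4/84}, with 84 students per arm. That is .17, .15, .13 and .11, well below the true SEs of .327, .302, .248 and .166. The conservative direction in step 3 therefore requires class-by-time variation in the model.

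**The case against.** The strongest reply is that the main matching variable is already in the model. Baseline MVPA is one of the occasions at the time level, and the abstract specifies a comparison of changes. Gender is also a model term, and it covers class gender if classes are single-sex, as matching on class gender suggests. Only the pair itself and the curriculum indicator are wholly absent. This stands, and it shrinks the problem: at ρ = .7 or above, the change analysis loses no visible power without the pair.

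Four stronger readings are tempting, and the document does not support them:

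- *The standard error is certainly too large, perhaps by 41%.* That figure belongs to a follow-up-only analysis with r = .5. The article does not give r. For change scores the simulated excess is 4 to 21%. With random intercepts only, the error would go the other way.
- *The matching is wasted.* It still balances the arms and lowers the true variance of the estimate. Only the credit for it in the standard error is lost.
- *The sample size is wrong because it uses an unmatched test.* The arithmetic reproduces, and 24 classes are adequate once r is about .1 or more.
- *Baseline MVPA is ignored.* It is in the outcome vector, though the section does not say through which term.

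An article may also leave the detail of random effects to a fuller plan. That excuses the silence on class-by-time variation. It does not explain a model whose levels and covariates are listed without the pairs.

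**Conclusion.** The point holds as a mismatch between design and analysis, of moderate size. The trial randomises within pairs, and the stated model has no pair and no curriculum indicator. If matching works and class-by-time variation is modelled, the test is valid but conservative. Without the pair, power falls from 79 to 70% at a class-level correlation of .3 and from 86 to 83% at .5, with no visible loss at .7 or .9. At .3 the unpaired change analysis falls below the planned 80%.

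These sizes rest on assumed correlations, balanced data, class means, and matching on gender and baseline MVPA only. The contribution of the curriculum indicator was not quantified.

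**What to change.** Under Statistical methods, specify one of two analyses for MVPA.

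1. **Group × time model with pairs.** State the group × time term as the treatment effect, and add a random intercept for pair together with class-by-time variation. Let the pair effect differ between baseline and follow-up, because one that is constant over time cancels from the change and cannot represent similarity of changes within a pair.
2. **Follow-up model.** Take follow-up MVPA as the response, with class-mean baseline MVPA, class gender and the curriculum indicator as class-level covariates.

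Use small-sample degrees of freedom in either case. The two are alternatives, not equivalents, and baseline MVPA must not be both response and covariate. Fixed pair effects should not be combined with a class gender term, since pairs are matched on gender and the two are collinear. The sample size can stay as it is.

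**Cost.** All matching variables are known before randomisation, so no data collection changes. The first option adds terms to the stated model; the second changes its response. Both use a few class-level degrees of freedom, and pairing loses a little power if the within-pair correlation is below about .1 (77.0% against 80.9% at zero, from step 2).
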